### Sample size for the intervention study

The minimum sample size for this study was obtained using the formula for calculating sample size for two proportions with the aim of detecting a difference in outcomes between the groups [23]. The effect size of a similar study which was conducted in Denmark [24] and the prevalence of moderate and high intensity physical activity reported by Odunaiya et al., 2010 [12] were used for calculating the minimum sample size. A multi-level intervention to promote physical activity among in-school adolescents has not been conducted in Nigeria and the effect size is unknown. This justifies the use of the value reported in Denmark [24]. A *multilevel intervention is defined as an intervention* that addresses at least three levels of the multilayer system. It target at least three sources of influence that may ultimately result in improved health behaviour and outcomes [25].

Intracluster correlation coefficient (ICC) is a measurement that captures between-cluster and within-cluster variability in outcome and is required for sample size calculation in clustered studies that comprise exposed or unexposed clusters [26–29]. To account for this, the intracluster class correlation reported by Oyeyemi et al., (2014) which assessed participants’ self-reported active transportation to school and leisure-time Moderate-to-Vigorous Physical Activity (MVPA) among in-school adolescents was used to estimate the within and between school variation in physical activity in order to control for clustering within the schools (ICC = 0.38) [30]. The formula is outlined below:$$ \mathrm{n}=\frac{{\left({Z}_{\alpha /2+}{Z}_{\beta}\right)}^2\left[{\mathrm{P}}_1\left(\ 1-{\mathrm{P}}_1\right)+{\mathrm{P}}_2\left(\ 1-{\mathrm{P}}_2\right)\right]}{{\left({\mathrm{P}}_{1\hbox{--} }{\mathrm{P}}_2\right)}^2}\times \left[1+\left({\mathrm{m}}_{\mathrm{o}}-1\right)\times \mathrm{ICC}\right]. $$where Z_α/2_ is the critical value of the normal distribution at α/2 (e.g. for a confidence level of 95%, α is 0.05 and the critical value is 1.96), Z_β_ is the critical value of the normal distribution at β (e.g. for a power of 80%, β is 0.2 and the critical value is 0.84) and P_1_ and P_2_ are the expected sample proportions of the two groups.

Z_α/2_ = 1.96 at 5% level of error.

Z_β_ = 0.84

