### Blinding and sampling technique

Multistage sampling technique will be used for the study. Nigeria is divided into six regions with approximately six states each. The south west region was purposively selected for this study.Step 1:The study state was selected randomly from the six states in the south west region of Nigeria.Step 2:Two comparable Local Government Areas (LGAs) in the project state will be selected using simple balloting. The list of LGAs was stratified based on their socio-economic status and level of urbanisation. One of the LGAs will be the experimental while the other will serve as the control.Step 3:The list of schools will be obtained for the selected LGAs and stratified by ownership i.e. public and private and population size. Twenty two schools will be pair-matched based on their ownership (i.e. public and private) and population size and randomly allocated to either the experimental (11 schools) or control (11 schools) group by simple randomisation by an independent researcher not involved in the study.Step 4:The male and female student ratio for the selected schools will be obtained and used for the determination of students to be selected for each school disaggregated by sex. The selected in-school adolescents will serve as the index children though all the students in the schools allocated to the experimental group will be exposed to the intervention.Step 5:The number of arms for classes from each school will be documented and two arms of classes at each level in the school will be selected by balloting for the study.Step 6:Study participants in each class will be selected using systematic random sampling technique based on the male to female student ratio and expected cluster size for the school.Step 7:The selected respondents will be enrolled as a cohort in the experimental and control schools and followed up after the 12-week intervention.

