### Data collection

The data collection will be at three time points the first will be at baseline (T0), the second will be immediately after the 12-week intervention (T1) while the third will be three months after the intervention (T2). Details in Table 1. The data collection will employ a mixed methods approach including:(i)A desk review of relevant state and national NCDs prevention policies and guidelines on physical activity and an assessment of the level of coherence of the School Health Promotion policy with these policies. Other documents which will be reviewed include the Physical Health Education curriculum and school timetable to assess the opportunities for PA during school hours. The policies which regulate the construction of schools will also be reviewed to assess the extent to which these documents regulates or influences the built environment and physical activity levels in school.(ii)Physical and Health Education Teachers will complete the School Physical Activity Policy Assessment tool (S-PAPA) – a standardised semi-structured tool which assesses physical education, recess and other physical activity opportunities before, during and after school [31]. For this study, only two components will be assessed - physical education and recess. Scores on the S-PAPA tool will be tabulated based on policies and practices identified as being related to children’s physical activity during school [32, 33]. Total point scores will also be either median-split into high- and low or stratified by percentile for analysis [34].(iii) Focus Group Discussions and In-depth interviews will be held with teachers and school principals respectively to assess their opinion about social norms and support and the extent of implementation of physical activity policies and programmes in schools, level of funding, and the frequency of engagement in structured physical activity. Observations will be conducted to document facilities for physical activity in the schools using the Sport, Physical Activity and Eating behaviour: Environmental Determinants in Young people (SPEEDY) checklist. The SPEEDY checklist measures the built environment of schools and can be scored to quantify environmental support for physical activity [35]. The checklist assesses school-level environmental variables such as *Walking Provision, Cycling Provision, Aesthetics, Sport and facility provision, Other facility and Design of the school grounds* [36] The scores from each of the key variables will be dichotomised into low and high based on percentiles, and the school physical activity suitability index will be computed [36, 37].(iv) A cross sectional survey will be conducted among the students using an adapted version of the *Physical Activity Questionnaire for Adolescents (PAQ-A)* [38] to generate self-reported data on the level of physical activity among young people. The PAQ-A is a self-administered, 7-day recall instrument. It was developed to assess general levels of physical activity for high school students approximately 13 to 19 years of age. It assesses the frequency of participation in physical activity during spare time, physical education period, lunchtime, after school, in the evenings and on weekends. A summary of the physical activity score is generated from the mean of 8 items, and ranges from 1 to 5, with higher scores indicating more frequent participation in physical activity [38]). The physical activity levels will be categorised into three; low physical activity level will be those who score between 1 to 1.9 while moderate and high physical activity levels will be those who score between 2 to 3.9 and 4 to 5 respectively [13]. For some statistical analyses, the self-reported physical activity level will be treated as a continuous variable. In a study to establish the convergent validity of the PAQ-A, the instrument was found to be significantly correlated to all self-report measures (including activity rating, *r* = 0.73; Leisure Time Exercise Questionnaire, *r* = 0.57; and 7-day physical activity recall interview, *r* = 0.59) [39]. The survey will also assess the frequency of engagement in structured physical activity from two time points (baseline and follow up) as the primary outcome measure. Based on the theory of Planned Behaviours which is the theoretical framework guiding this intervention, other variables which will be incorporated into the Physical Activity Questionnaire for Adolescents (PAQ-A) are the measures for attitude, subjective norms, perceived behavioural control and self-efficacy. A research tool which was theoretically derived by Motl et al., 2000 based on Theory of Reasoned Action (TRA) and Planned Behaviour (TPB) and Social-Cognitive Theory (SCT) will be used to assess the social-cognitive factors among this young people. This questionnaire has been tested and evidence provided for its factorial validity as a unidimensional measure of attitudes, subjective norms, perceived behavioural control and self-efficacy about physical activity among adolescent girls [40]. The core variables i.e. *knowledge of health benefits of physical activity, attitude, subjective norms, perceived behavioural control and self-efficacy about physical activity* will be analysed by scoring and summing up all question items and cut-offs will be determined using percentiles.The survey will be complemented with focus group discussions to assess their opinions about the individual, social, community, institutional and policy factors which influences the physical activity behaviours of young people.(v)Anthropometric and other physical measurements (body-mass-index for age, waist-to-hip ratio, blood pressure) will be documented. Anthropometric measurements will be taken twice and averaged; for discrepancy >10%, a third measurement will be taken. The height and weight will be assessed using standard anthropometric procedures. Height will be measured using a portable height meter/stadiometer. Students will be asked to take off their shoes and stand with their back to the portable height meter/stadiometer. The sliding bar will be lowered and pressed flat on the head and recorded to the nearest centimeter. Body weight will be measured using a digital scale and weight will be recorded to the nearest gram. Age -and sex -specific prevalence of overweight and obesity will be determined by the body-mass- index for age Z scores using the criteria defined by the World Health Organisation (WHO). According to the WHO cut off points; overweight is considered to be > + 1SD (equivalent to BMI 25 kg/m2 at 19 years), Obesity: > + 2SD (equivalent to BMI 30 kg/m2 at 19 years), Thinness: <-2SD, Severe thinness: < −3SD and Normal: > −1 to < +1 SD. Standard deviations (Z-scores) will be computed using the World Health Organisation (WHO) reference population, 2007 soft ware (Anthropometric Software Program, Version 1.0.4 [41]. Blood pressure will be measured and the mean of three measurements will be recorded. Referrals will be initiated for children whose blood pressure exceeds the 95th percentile for age. Waist circumference will be measured to the nearest 0.1 cm horizontally at the narrowest point between the lower end of the rib cage and iliac crest. Hip circumference will be measured to the nearest 0.1 cm, at the greatest horizontal circumference below the iliac crest at the level of greater trochanter. Waist hip ratio will be obtained as waist circumference/hip circumference.The fitness level of the adolescents will be measured using the 20-m shuttle run test (20-mSRT) also known as the multi-stage fitness test. The 20-mSRT is the most widely used field-based test for aerobic fitness in young people and UK percentile data and health-related cut points are available [42]. A systematic review recently concluded that the 20-mSRT is the most reliable and valid field based method to estimate aerobic fitness in young people [43]. Performance in the 20-mSRT is typically expressed as laps, levels or distance completed. The 20mSRT estimates the cardiorespiratory fitness (aerobic capacity). Children run back and forth between two lines 20-m apart following beep signals played from a pre-recorded CD. The pace of the test is ramped such that running speed increases by 0.5 km/h each minute or period. The test is finished when the child stops owing to fatigue or when he/she does not reach the line in time with the audio signal on two consecutive occasions [44]. The last completed run indicates the final result of the test. The physical fitness data will be analysed and used as continuous variables and an increase in test results will indicate higher physical fitness [45].(vi) Step count will be recorded using a pedometer. During the data collection process, 100 students (10% of the sample) will be asked to wear a Yamax SW200 Step Digi-Walker pedometer on their right hand for seven consecutive days, except during sleep and water based activities. Text messages/phone calls will be made daily as reminders to ensure compliance. The pedometers will be sealed with a sticker or cable to prevent reactivity i.e. a situation where individual change their normal activity pattern as a result of being monitored.The pedometers will be worn daily for seven days with a minimum of 4 valid days. Step counts of less than 1000 steps per day and greater than 30,000 steps per day will be treated as missing data [46]. Step count of 10,000 to 11,700 and over will be recorded as achieving the daily recommended levels of 60 min of MVPA in adolescents [47].

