Regression analysis will be used to assess the extent to which the independent variables predict self-reported physical activity levels and step count (average steps/day). Level of significance will be 5% at 95% confidence interval. The effect of the intervention will be tested using multilevel mixed effects models for repeated measures adjusted for relevant confounding factors. This approach ensures that the longitudinal and hierarchical structure of the data are considered in the analysis. Because of the clustered structure of the data, random effects for the cities and schools will be included in all analyses.

The qualitative data will be transcribed, coded, entered into NVIVO version 10 and analyzed using thematic approach. Points of agreement and disagreement among discussants with reference to the study objectives will be noted.

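### Read as intercepts, the named school random effects leave between-school variation in change out of the intervention test; for self-reported activity this can push type I error well above 5% if schools drift differently

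*Protocol article*

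**What the plan says.** All of this is in the protocol article.

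- **Effect model** (Data management and statistical analysis): "The effect of the intervention will be tested using multilevel mixed effects models for repeated measures adjusted for relevant confounding factors". The section adds: "This approach ensures that the longitudinal and hierarchical structure of the data are considered in the analysis".
- **Random effects** (same section): "Because of the clustered structure of the data, random effects for the cities and schools will be included in all analyses". No student term, random slope or school-by-time term is named. The fixed effects and the contrast that carries the intervention effect are not written out.
- **Error rate** (same section): "Level of significance will be 5% at 95% confidence interval".
- **Design** (Blinding and sampling technique): schools are pair-matched and "randomly allocated to either the experimental (11 schools) or control (11 schools) group by simple randomisation". The sampled students form a cohort and are followed up.
- **Timing** (Data collection; Tables 1 and 2): both primary outcomes are measured at T0, at T1 (end of the 12 weeks) and at T2 (three months later).
- **Clustering input** (Sample size for the intervention study): one ICC, taken from another study, "to control for clustering within the schools (ICC = 0.38"). It describes a single time point. No figure is given for how much schools differ in change.

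**The concern.** With baseline among the repeated outcomes, the natural measure of effect is the difference between arms in change from T0 to T1 or T2. A school or city intercept is the same at every visit, so it drops out when T0 is subtracted. What remains in the standard error is residual variation spread over about 500 students per arm, as if students in one school changed independently of one another.

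That is right only if all schools would change by the same amount without the intervention. Self-reported activity is a seven-day recall that covers physical education, lunchtime and after-school periods, so one school's timetable in the measurement week could shift all its students together. With 11 schools per arm, such shifts do not average out as fast as the model assumes. The risk is that ordinary differences between schools in term-to-term change are declared an intervention effect, with confidence intervals that are too narrow.

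**Working it through.** **Inputs from the protocol article.** 11 schools per arm; 500 students per arm, so m = 500/11 = 45.5 per school; ICC 0.38; two-sided 5% (1.96). Pedometers: 100 students, so m = 100/22 = 4.5 per school if spread evenly (the spread is an assumption).

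**Assumptions not in the documents.** Cluster autocorrelation (CAC, the correlation over time of a school's true level) from 1.0 to 0.8. Student autocorrelation r = 0.5, varied from 0.3 to 0.7. Total variance is set to 1 and the outcome is treated as continuous.

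**Variance components.**
- School-by-time: s = ICC × (1 − CAC)
- Residual: e = (1 − ICC) × (1 − r)

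**Variance of the arm difference in change (T1 − T0), k schools per arm.**
- True: (4/k) × (s + e/m)
- Model with student and school intercepts: (4/k) × (s + e)/m
- Model with school intercepts only: (4/k) × (s + 1 − ICC)/m

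D is the true variance divided by the model variance. Type I error = 2 × [1 − Φ(1.96/√D)].

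**Worked case: self-report, ICC 0.38, CAC 0.8, r = 0.5.** s = 0.38 × 0.2 = 0.076 and e = 0.62 × 0.5 = 0.31.
- Student and school intercepts: D = (0.076 + 0.31/45.5) / [(0.076 + 0.31)/45.5] = 0.0828/0.00849 = 9.75. The standard error is too small by √9.75 = 3.1 times. Type I error is 53%.
- School intercepts only: D = 0.0828 / [(0.076 + 0.62)/45.5] = 0.0828/0.0153 = 5.41. Type I error is 40%.

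**Type I error at r = 0.5.** With student and school intercepts, CAC 1.0 reproduces the plan's nominal 5%.

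| Outcome and ICC | Random intercepts | CAC 1.0 | 0.95 | 0.9 | 0.8 |
|---|---|---|---|---|---|
| Self-report, 0.38 | student + school | 5% | 30% | 42% | 53% |
| Self-report, 0.38 | school only | 0.6% | 15% | 27% | 40% |
| Self-report, 0.10 | student + school | 5% | 11% | 16% | 25% |
| Self-report, 0.10 | school only | 0.6% | 2% | 5% | 11% |
| Self-report, 0.05 | student + school | 5% | 8% | 11% | 16% |
| Pedometer, 0.38 | student + school | 5% | 7% | 10% | 13% |
| Pedometer, 0.38 | school only | 0.6% | 1.3% | 2.2% | 4.3% |

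**Sensitivity to r (0.3 to 0.7, ICC 0.38).**
- Self-report, student and school intercepts: 25–39%, 36–50% and 48–60% at CAC 0.95, 0.9 and 0.8.
- Self-report, school intercepts only: 13–17%, 25–28% and 39–41%.
- Pedometer at CAC 0.8: 11–17% with student and school intercepts, 2.5–6.4% with school intercepts only.

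**Simulation check** (4,000 runs, 45 students per school, ICC 0.38, r = 0.5, student and school intercepts). Two time points: 28%, 42% and 53% at CAC 0.95, 0.9 and 0.8. Three time points, T1 contrast: 29%, 42% and 53%. A t-test on the 22 school mean changes (20 degrees of freedom) stayed between 4.4% and 5.9% in every scenario run.

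**The case against.** The strongest reply is that the article does not say what this point attributes to it. It does not describe the school effects as intercepts, does not exclude a school-by-time term, and names no arm-by-time test. Covariance structure is often left to an analysis plan, and one may exist. It is true that these are readings. But the article does more than stay silent: it lists the random terms and says that the approach deals with both the longitudinal and the hierarchical structure. Intercepts are the ordinary meaning of that list. If a pooled arm effect over all visits was meant instead, it would mix in pre-intervention data, and the wording would still need work.

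Three stronger conclusions are tempting, and the documents do not support them.

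- *That type I error is necessarily far above 5%.* It depends on how differently schools drift, which the documents do not quantify. The ICC of 0.38 is cross-sectional and cannot supply that figure. Without drift the test holds 5%, and it is conservative if no student term is fitted.
- *That both primary outcomes are affected alike.* With about 4.5 pedometer wearers per school, the inflation is modest or absent.
- *That the secondary outcomes share the problem to the same degree.* Table 4 lists nearly all of them as ordered categorical, and no ICC is given for them; they were not calculated.

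It is also fair to object that the higher figures need a student intercept, which the article does not name. Both models are therefore shown.

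**Conclusion.** The point holds in conditional form. Followed as it naturally reads, the model tests change without letting schools differ in change, and for self-reported activity this can badly understate uncertainty. At ICC 0.38 and r = 0.5, type I error is about 28–53% with student and school intercepts and about 15–40% with school intercepts only, for CAC from 0.95 to 0.8. Even CAC 0.99 gives 11% with student and school intercepts. At ICC 0.10 the corresponding ranges are 11–25% and 2–11%. For pedometer steps, inflation at r = 0.5 is at most about 13%, and absent with school intercepts only.

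These sizes rest on assumed autocorrelations, a linear model for a continuous score, and an ICC borrowed from a different activity measure. The mechanism does not depend on them. How the city effect is handled is a separate matter, and settling it would not restore the missing variation.

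**What to change.** In Data management and statistical analysis, replace the general reference to school random effects with random intercepts for student and school plus a random school-by-time effect. Name arm-by-T1 and arm-by-T2 as the intervention contrasts.

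A different but also acceptable model analyses T1 and T2 with the T0 value as a covariate and a school random effect. It conditions on baseline and is not the same model, so one of the two should be chosen in advance.

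In either case, state that the reference degrees of freedom come from the number of schools (20 for a simple comparison of 22 school mean changes), not from students.

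The cost is one extra random term and no new data. Confidence intervals widen by as much as schools really differ in change. For self-report at ICC 0.38 and r = 0.5, against student and school intercepts, the standard error grows by √3.57 = 1.9 times at CAC 0.95 and 3.1 times at CAC 0.8. With no drift it is essentially unchanged.

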## Conclusion

This protocol outlines the rationale and description of a multi-level, multi-component, cluster randomised controlled trial study designed to improve the physical activity behaviours of in-school adolescents in south western Nigeria. The study is underpinned by the socio-ecological model and participatory research principles which involve study beneficiaries (adolescents) in the design of the intervention taking into cognizance the extraneous policy and environmental factors which influences their behaviours.

